## Abstract

**Background:**

Childhood dental anxiety is very common, with 10–20 % of children and young people reporting high levels of dental anxiety. It is distressing and has a negative impact on the quality of life of young people and their parents as well as being associated with poor oral health. Affected individuals may develop a lifelong reliance on general anaesthetic or sedation for necessary dental treatment thus requiring the support of specialist dental services. Children and young people with dental anxiety therefore require additional clinical time and can be costly to treat in the long term. The reduction of dental anxiety through the use of effective psychological techniques is, therefore, of high importance. However, there is a lack of high-quality research investigating the impact of cognitive behavioural therapy (CBT) approaches when applied to young people’s dental anxiety.

**Methods/design:**

The first part of the study will develop a profile of dentally anxious young people using a prospective questionnaire sent to a consecutive sample of 100 young people referred to the Paediatric Dentistry Department, Charles Clifford Dental Hospital, in Sheffield. The second part will involve interviewing a purposive sample of 15–20 dental team members on their perceptions of a CBT self-help resource for dental anxiety, their opinions on whether they might use such a resource with patients, and their willingness to recruit participants to a future randomised controlled trial (RCT) to evaluate the resource. The third part of the study will investigate the most appropriate outcome measures to include in a trial, the acceptability of the resource, and retention and completion rates of treatment with a sample of 60 dentally anxious young people using the CBT resource.

**Discussion:**

This study will provide information on the profile of dentally anxious young people who could potentially be helped by a guided self-help CBT resource. It will gain the perceptions of dental care team members of guided self-help CBT for dental anxiety in young people and their willingness to recruit participants to a trial. Acceptability of the resource to participants and retention and completion rates will also be investigated to inform a future RCT.

## Background

Dental anxiety is common, affects people of all ages [1], and tends to develop in childhood and adolescence [2, 3]. The prevalence of severe dental anxiety in children ranges from 5 to 20 % in different countries and age groups [4–6]. Dental anxiety impacts on the quality of life of young people with those affected reporting significantly worse oral health-related quality of life, with particular impact on social and emotional well-being such as feeling upset or worried or being teased or left out [7]. Young people with high levels of dental anxiety also have more decayed and extracted teeth [8, 9] and demonstrate increased unmet need for dental care [10, 11] as compared to their peers with low levels of anxiety and who are regular attenders. Up to one in five young people reports not visiting the dentist regularly because of fear [12]. Fear is also a significant barrier to completion of dental treatment [13]. Research has found that children who are most likely to have missed previous dental appointments were those who were rated by their parents as having high levels of dental anxiety [14]. Hallberg and colleagues [15] found that parents experienced difficulties trying to persuade their dentally anxious children to go to their dental appointment and felt they lacked strategies to handle their child’s level of fear and effectively manage the situation [16].

Dental anxiety in young people also has a significant impact on dental services. Providing treatment for anxious patients is time consuming, costly, demanding, and a cause of occupational stress for dentists [17]. These factors result in patients being referred to secondary care services, having to wait longer for dental treatment and increased costs to the National Health Service (NHS) [18].

Traditionally, dental anxiety has been managed using pharmacological techniques including inhalational sedation and general anaesthetic (GA). However, such approaches only manage rather than reduce children’s dental anxiety [19]. The cost per case for inhalational sedation or GA for dental treatment has been estimated at £273 and £720, respectively [20]. Indeed, dental anxiety remains unchanged in those children who receive dental treatment under GA [21] with anxious children becoming adults with a long-term reliance on expensive interventions in specialist settings.

Over recent years, it has been recognised that greater effort should be directed towards behaviour management and psychological interventions which can reduce the patient’s anxiety in the long term [22, 23]. Advances in the treatment of anxiety in young people have been made in the field of cognitive behavioural therapy (CBT), including self-help approaches. CBT is a goal-orientated talking therapy which aims to help people manage their problems by changing how they think and behave in relation to their problems. It is a type of therapy which can be used to teach patients (and often their parents/carers) skills for the self-management of their anxiety. CBT incorporates a variety of different cognitive and behavioural strategies which aim to help the patient modify the unhelpful behaviours or thoughts maintaining their anxiety [24].

A review of meta-analyses revealed that CBT is highly effective in treating a range of anxiety disorders in both children and adults [25, 26]. Behavioural interventions, such as graded exposure and systematic desensitisation to feared stimuli, have been found to be effective in reducing dental anxiety levels of children [27–29]. Studies have also found modelling interventions, which help patients develop effective coping skills by observing other people (e.g. other children, parents) successfully receiving dental treatment (film, in vivo), are effective in improving the behaviour of dentally anxious young people [30]. Whilst there has been a paucity of research investigating the effectiveness of cognitive-behavioural interventions in reducing young people’s dental anxiety, research has revealed promising results in the use of such strategies to reduce adults’ dental anxiety [31, 32].

Based on (1) evidence for the effectiveness of self-help CBT for young people with general anxiety; (2) case studies of CBT for children with dental anxiety [33, 34]; and (3) experience from the use of CBT for dental anxiety in adults including CBT delivered by dental nurses in Sheffield, there was sufficient evidence to suggest that a self-help CBT resource for young people with dental anxiety could be highly effective at reducing dental anxiety and its consequences. However, no such resource had been evaluated to date.

### Aims of study

The study will determine the feasibility of evaluating, in a randomised controlled trial (RCT), a CBT resource for young people (aged 9–16 years) for the reduction of dental anxiety.

It will specifically:Identify a profile of dentally anxious young people who could potentially be helped by a guided self-help CBT resourceExplore perceptions of primary dental care team members of guided self-help CBT for dental anxiety in young people and their willingness to recruit participants to a future substantive trialEvaluate the retention and completion rates and acceptability of the guided self-help CBT resource to patients and parentsIdentify potential outcome measures for use in a future RCTDetermine the sample size required for a future RCT

## Methods/design

This mixed-method study will be conducted in three phases to allow the objectives to be achieved and to capture the perspectives of all relevant stakeholders. For each phase the design, procedure and approach to data analysis will be described. Ethical approval will be obtained from an NHS research ethics committee.

### Intervention

The intervention will be a self-help paper-based CBT resource developed with young people, parents, and dental professionals based on the Five Areas model of CBT [24] which uses a combination of cognitive and behavioural techniques to reduce dental anxiety. The resource will be given to young people by a dentist who will guide them through the use of it during dental appointments. More information about the resource can be found at https://www.sheffield.ac.uk/dentalschool/research/create/research_projects.A)
***The profile of dentally anxious young people***

**Design of the study**
This part of the project will develop a profile of dentally anxious young people who could potentially be helped by a self-help CBT resource to reduce dental anxiety. It will include a prospective questionnaire sent to a consecutive sample of 100 young people referred to the Paediatric Dentistry Department in Sheffield for the management of dental anxiety. The questionnaire will include items to establish patient demographic information, quality of life (the Child Health Utility 9D) [35], level of dental anxiety (Modified Child Dental Anxiety Scale) [36], any psychological disorders (Revised Child Depression and Anxiety Scale and the Strengths and Difficulties Questionnaire) [37, 38], and willingness to consider using a CBT resource. The findings will allow an estimate to be made of the number of young people and their parents who could potentially be helped by a guided self-help CBT resource and that would need to be assessed in order to identify sufficient patients who are eligible and willing to take part in a future trial.
**Setting and recruitment**
Suitable child patients will be identified by a clinician member of the study team by screening of referral letters to the Paediatric Dentistry Department according to the inclusion/exclusion criteria described below. The questionnaire will be posted to potential participants, with covering letters and Participant Information Sheets for both the young person and their parent/carer. Young people will be involved in the design of the covering letter and Participant Information Sheets. Parents/carers will be invited to help their child complete the questionnaire if necessary. If young people and their parent consent for them to take part, they will be asked to return the completed questionnaire when they attend for their appointment. In order to maximise the response rate, if the participants have not completed their questionnaire when they attend for their appointment, they will be given a copy to complete at the appointment and sufficient time to do this in a private area of the clinic. Based on previous surveys in the department, a response rate of 60 % is anticipated. Participants will continue to be recruited until the sample size of 100 is achieved. Recruitment will be restricted to those aged 11–16 years due to the length of the questionnaire which takes around 15 min to complete and the nature of some of the questions about depression and anxiety.

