**Sample size**
The sample size has been based on a similar questionnaire survey of 100 adults attending a clinic for patients with dental anxiety at a dental hospital in London [39].

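### Part A questionnaires are collected only through an attended appointment, so the profile may be selected towards attenders; the count of 100 sent also needs rewording as 100 completed

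*Protocol article*

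**What the plan says.** Part A (the profile of dentally anxious young people) is a descriptive survey.

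- **Collection.** Under Setting and recruitment, the questionnaire is posted, and consenting families "they will be asked to return the completed questionnaire when they attend for their appointment". Anyone who arrives without it is given another copy and time to complete it in clinic. The article describes no other route.
- **Count and response.** The same section states that "a response rate of 60 % is anticipated" and that "Participants will continue to be recruited until the sample size of 100 is achieved". The Sample size section adds: "The sample size has been based on a similar questionnaire survey of 100 adults attending a clinic for patients with dental anxiety".
- **Count elsewhere.** Design of the study describes "a prospective questionnaire sent to a consecutive sample of 100 young people referred to the Paediatric Dentistry Department in Sheffield". The abstract likewise has a "prospective questionnaire sent to a consecutive sample of 100 young people".
- **Anxiety and attendance.** The Background reports, with reference to dental anxiety: "children who are most likely to have missed previous dental appointments were those who were rated by their parents as having high levels".
- **Use of the result.** Design of the study says the findings will be used to estimate how many young people could be helped by the resource, and how many would have to be assessed to find enough eligible and willing patients for a future trial.

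**The concern.** A child who does not come to the appointment has no described way to enter the data. By the protocol's own evidence, not coming is related to the trait being profiled. Continuing until 100 are in hand brings in more attenders. It reaches the target without recovering the missing group, and the more children who are missed, the less visible the loss becomes in the final count.

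What is at stake is the planning use. The number to be assessed for a future trial is a yield per referred child, but it would be estimated from those who attended and responded. Anxiety level, psychological screening results and willingness to use the resource are all collected on this questionnaire, so any of them could be affected.

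A second, smaller matter is the figure of 100, which appears both as the number the questionnaire goes to and as the number obtained. With 60% response it cannot be both.

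**Working it through.** **1. The count**

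Inputs: 100 sent (abstract; Part A, Design of the study); 60% response and recruitment until 100 is reached (Part A, Setting and recruitment). The 100 comes from an earlier survey (Sample size), so there is no formula to reproduce. The check is whether the statements agree.

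- If 100 are sent: 100 × 0.60 = 60 returned, not 100.
- If 100 are to be returned: 100 / 0.60 = 166.7, so about 167 sent, not 100.
- Sensitivity to the response rate (50% and 70% are assumed): 100 / 0.50 = 200; 100 / 0.70 = 142.9, about 143.

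Precision for a proportion near 50%, as a 95% half-width:

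- n = 100: 1.96 × √(0.25/100) = 0.098, or 9.8 points.
- n = 60: 1.96 × √(0.25/60) = 0.127, or 12.7 points.

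The stopping rule and the Sample size section both point to 100 respondents, so the 9.8-point figure is the relevant one.

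**2. The return route**

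| Step described in Part A | Needs attendance? |
|---|---|
| Questionnaire posted | No |
| Completed copy handed in | Yes |
| Back-up copy completed in clinic | Yes |
| Further recruitment up to 100 | Yes, by the same two routes |

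The Background sentence supplies the link between the last three rows and the variable measured.

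**3. How large could the effect be?**

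Let *a* be the share of those mailed who attend, *pA* the proportion with some feature among attenders and *pN* the proportion among non-attenders. The proportion in all those mailed is *a·pA + (1 − a)·pN*, so an attenders-only estimate is off by (1 − *a*) × (*pA* − *pN*).

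The documents give neither *a* nor the difference. As an illustration only, assume a difference of 20 points:

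| Assumed attendance | Error of the attenders-only estimate |
|---|---|
| 90% | 0.10 × 20 = 2 points |
| 80% | 0.20 × 20 = 4 points |
| 70% | 0.30 × 20 = 6 points |
| 60% | 0.40 × 20 = 8 points |

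The sign follows the sign of *pA* − *pN*. The number finally recruited does not appear in the formula, so reaching 100 leaves the error unchanged.

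To see the planning consequence, suppose 50% of attenders but 30% of non-attenders are eligible and willing (assumed). The true proportion is then 48% at 90% attendance and 42% at 60% attendance. To find 100 participants, the attenders-only figure suggests assessing 100 / 0.50 = 200 referred children. The need would be 100 / 0.48 ≈ 208 and 100 / 0.42 ≈ 238 respectively.

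**The case against.** **The count is loose wording.** The recruitment section governs recruitment, and its stopping rule is explicit. This stands. A reader might infer that staff could stop at 100 mailings and be left with about 60 returns and a half-width of 12.7 points. The stopping rule and the stated basis of the 100 make that unlikely.

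**The absence of other routes is inferred from a condensed article.** A fuller protocol may contain a reminder or a postal return, and nothing here says that a child who misses one visit and attends a later one is excluded. This stands in part. However, the section sets out posting, return and back-up in some detail and offers the clinic copy as its way of raising response, so the described procedure can fairly be judged as written.

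**Attenders are close to the right population.** The resource is given out and guided by a dentist at appointments (Intervention), so persistent non-attenders could hardly use it. Part A is also limited to mild to moderate anxiety (Type of participants). Both points moderate the effect without removing it. Missing one appointment is not permanent non-attendance, anxiety varies within that range, and Part A eligibility is screened from referral letters while the anxiety scale is in the questionnaire itself. The count of referrals to be assessed is affected in any case.

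**The direction is not proven.** A reader might infer that anxiety will certainly be understated. The Background reports an association with parent-rated anxiety. In children already referred for anxiety, and limited to the mild-to-moderate range, it could be weaker. Understatement is the likelier direction, no more.

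**Conclusion.** The concern holds in a moderate form. The collection procedure, as described, selects on attendance, the protocol itself links attendance to anxiety, and recruiting until 100 is reached does not correct this. The profile and the number of referrals to be assessed may be tilted towards attenders, probably towards lower anxiety.

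The size of the bias cannot be computed, because no attendance rate is given. The 2 to 8 points rest on an assumed 20-point difference and assumed attendance of 90% to 60%; they show scale and are not estimates. It is tempting to apply a difference to the whole 40% expected not to respond: 0.40 × an assumed 10 to 30 points gives 4 to 12 points, which at its upper end passes the 9.8-point sampling error. The documents do not support that step. Some of the 40% will be children who attend and decline, and the share who do not attend is unknown.

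The count is a separate and minor matter: 100 completed is the operative target, and two sentences need correcting.

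**What to change.** 1. Enclose a prepaid return envelope with the posted questionnaire, and send one reminder to those who do not attend.
2. Record how many were mailed, how many attended and how many returned a questionnaire, and report the response rate.
3. Compare responders with non-responders, in aggregate, on non-identifying variables already held, such as age and sex. The documents do not say that referral letters record deprivation, so the comparison should not depend on it.
4. If a gap remains, limit the conclusions to young people who attend, and say so where the number to be assessed for the future trial is derived.
5. In the abstract and in Part A, Design of the study, replace the statement that the questionnaire goes to 100 with 100 completed questionnaires, about 167 sent at the anticipated 60% response.

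The cost is postage and a little administration. Items 1 and 2 need to be in place before mailing starts, since the missing returns cannot be fully recovered afterwards. Item 5 is an edit to the text.

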**Sample size**
The sample size has been based on a similar questionnaire survey of 100 adults attending a clinic for patients with dental anxiety at a dental hospital in London [39].
**Type of participants**
The following inclusion and exclusion criteria will be adopted:
*Inclusion criteria*
Children aged 11–16 years old with mild to moderate dental anxietyChildren referred to the Paediatric Dentistry Department by a primary or secondary dental care provider for the management of dental anxiety

*Exclusion criteria*
Children who are unable to complete a questionnaire due to learning or language difficulties

**Data analysis**
Data will be entered into an electronic database (Statistical Package for Social Sciences, v20) and analysed using simple descriptive statistics.

B)
***The perceptions of dental care team members***

**Design of the study**
This part of the study involves a qualitative study of the perceptions of primary and secondary dental care team members of the developed self-help CBT resource and their willingness to recruit participants to a trial and potentially offer the resource to their own patients. This will be accomplished through conducting and analysing individual interviews.Face-to-face individual or group interviews will be conducted with members of the primary and secondary care dental care teams using a topic guide as the framework for the interview. A combination of individual and group interviews will be employed to gain a breadth and depth of information and at the convenience of the participants. The topic guide will be developed based on the theory of planned behaviour to explore the key barriers and facilitators (e.g. attitudes, perceived behavioural control, subjective norms) which may influence dental team members’ intentions to use a self-help CBT resource with their patients in future [40]. The interviews will be digitally recorded and transcribed verbatim as quickly as possible after the event and the recordings deleted after a short time. All identifying information will be removed from the transcripts to ensure anonymity.
**Setting and recruitment**
The research participants will be recruited from general dental practices, the salaried dental service, and secondary dental care in South Yorkshire. Participants will be purposively recruited to include dental practices serving varying levels of deprivation and ethnic minorities. The goal of purposive sampling will be to provide a range of experiences and views. Sufficient participants should be involved to achieve saturation of information but not so many to prohibit detailed analysis. It is expected that 15–20 dental care professionals will be interviewed.Identification: practices will be identified from the list of providers in South Yorkshire.Approaching: potential participants will be sent written information in the post.Recruitment: after the initial approach, the dental care professional will then be contacted by telephone by a researcher, after being given at least 1 week to consider whether or not they want to take part, with the aim of arranging a date for the interview. Written consent will be obtained on the day of the interview. Interviews will be conducted by trained researchers with both dental and social science backgrounds to reduce the risk of influencing the results. Dental care professionals will be given thank-you vouchers in gratitude for their time.

**Sample size**
As a qualitative approach is being used, no formal sample size calculation has been carried out. Based on previous experience, a maximum of 20 participants is likely to be required to achieve saturation [41, 42]. Recruitment will continue until no new themes emerge.
**Type of participants**
The following inclusion and exclusion criteria will be adopted:
*Inclusion criteria*
Dental professionals who are primarily employed in general dental practice or the salaried dental service in SheffieldDental professionals who provide dental treatment to children and young peopleDental professionals who have made a referral to a secondary dental care provider for the management of dental anxiety of a child or young person

*Exclusion criteria*
Dental professionals who do not treat children aged 9–16 yearsDental professionals who do not provide NHS treatment

